## Abstract

Violence against women (VAW) is common in Ghana, with nation-wide surveys reporting high prevalence of intimate partner violence (IPV) (physical, sexual and/or emotional violence). Our trial assesses the community level impact of the Rural Response System which uses Community-Based Action Teams ‘COMBAT’ for preventing VAW in Ghana. This study is a mixed method unmatched cluster randomised controlled trial and includes rural (n = 23), peri-urban (n = 7) and urban (n = 10) communities in four districts of the Central Region, Ghana. The trial will last three years with one baseline survey, one impact assessment and a qualitative baseline, midpoint and endline evaluation. A total of 40 localities were selected to serve as clusters (20 per trial arm) with about 82 households per cluster recruited at baseline. The same number will be recruited post-intervention. Adult women (18 to 49 years) and men (≥ 18 years) were drawn from different localities. Sampling of households within a community was random and done using a computerised system. In each selected household, one female or male resident was invited to participate. Individuals are eligible for inclusion in the study if they usually live (sleep and eat) in the household, have lived in the community for at least a year, and are between the ages of 18-to-49 years old. Our impact assessment component will compare past 12 months incidence of IPV (i.e. IPV experiences for women and perpetration of physical and/or sexual IPV for men) between arms in the trial. The implementation of this community trial comes at an opportune time when evidence on the effectiveness of a targeted VAW intervention in the Ghanaian society is needed to inform the development of national policies for preventing VAW. Our progressive research approach using a mixed method design will further extend knowledge globally on a multifaceted intervention to reduce the incidence of intimate partner violence in a developing country.

## Background

Violence against women (VAW) is a global public health burden that has significant consequences for women’s mental and physical well-being, including their reproductive and sexual health [1–5]. Intimate partner violence (IPV), which describes physical, or emotional, or sexual assault, or both, of a spouse or sexual partner, is a common form of VAW in many parts of the world [6], including Ghana [4,5,7–9]. A national study in 1998 revealed that 33% of Ghanaian women experienced physical violence at the hands of their current or previous partners, 29% had their first experience of sexual intercourse by force, whilst 33% of the women had been touched inappropriately against their will [7]. Findings from the Ghana Demographic Health Survey (GDHS) further indicate that among women aged 15–49 years, 36.6% reported experience of physical violence since age 15, 17.2% reported experience of violence in the 12 months preceding the survey and 18.8% reported lifetime experience of sexual violence [8]. Among ever-married women, the GDHS data showed that 34.9% have experienced some form of violence (physical, sexual, or emotional) by a husband or partner in the 12 months preceding the survey [8].

Estimates of IPV prevalence in Ghana have been steadily increasing over the years. In 2011, the UN Women’s violence against women prevalence survey in Ghana reported that between 13% and 61% of ever partnered women in Ghana have experienced a spectrum of lifetime physical violence [9]. While the main perpetrators of physical and sexual violence against women tend to be current or previous husbands and partners; strangers, teachers, schoolboys, other family members and acquaintances may also be perpetrators of physical and sexual violence [4,8]. Violence against women in Ghana is influenced by several factors, including social, economic and legal elements [3,5]. Existing data from the Ghana AIDS Commission (GAC) suggest that Ghanaian women often experience relative powerlessness, compared with men, because of poor economic empowerment and negative social norms [10]. As a result, they are often subject to the will of their partners and husbands. This powerlessness, along with limited life choices, makes it difficult to decline sexual advances without facing coercion or violence [10].

Although there have been very few nation-wide VAW prevalence studies in Ghana leading to limited empirical evidence on which prevention strategies could be based, VAW continues to be a growing public health issue in Ghana [7–10]. The absence of data pertaining to a long-term impact assessment of VAW interventions is therefore a key gap in VAW research in Ghana. For instance, even though the Rural Response System (RRS) which uses a community response model (Community-Based Action Teams ‘COMBAT’) for preventing VAW was developed in 2002 and subsequently piloted for two years in three communities (located in the Eastern, Ashanti and Upper East Regions of Ghana), an impact evaluation of the intervention was not done. After the first two years of implementation, the intervention was scaled up in 15 other communities for three more years (2005 to 2008), in the Eastern region, Ashanti, Upper East and Upper West Regions of Ghana. However, there has been no follow up in these beneficiary communities since 2008 to assess the long-term impact of the RRS [7]. An integral component for the success of the RRS is stakeholder buy-in, hence training sessions on VAW and support systems were held for state agencies mandated to handle VAW cases (i.e. the Police/Domestic Violence and Victim Support Unit (DOVVSU), Department of Social Welfare (DSW), Commission on Human rights and Administrative Justice (CHRAJ) and Ghana Health Service (GHS). Unfortunately, there has been no assessment of the district level capacity-building training sessions undertaken for staff of the state agencies. This trial assesses the impact of the Rural Response System intervention delivered to all adult women and men living in selected districts in the Central Region of Ghana.

## Methods

### Aim and objectives

The overall aim of this trial is to evaluate a multi-faced community intervention to reduce the incidence of IPV in selected communities in Ghana. Regarding the RRS model, the specific objectives of the impact assessment will be as follows:
To evaluate the impact of the RRS model in preventing/reducing VAWTo determine whether RRS intervention is effective in enabling women in to reduce their exposure to IPV and men to reduce their perpetration of IPVTo assess the extent to which RRS has changed individual attitudes about gender inequalityTo determine if the RRS model changes discriminatory social norms and gender roles which consider VAW acceptableTo examine state institutional response to reported cases of VAWTo assess whether the RRS model facilitated a shift in power relations between men and women in the household/community to become more equitable

### Study design

The study is a mixed method unmatched cluster randomised controlled trial with two arms. The intervention arm receives the rural response system (RRS) intervention for preventing VAW for 18 months while the control arm received no intervention. Owing to the nature of the intervention, participants will not be blind to their trial arm. Sampling of participants will follow a repeat-cross-sectional community survey. The trial is being conducted over 36 months with one quantitative and qualitative baseline assessment (2016) and one qualitative midpoint evaluation (2017). The impact assessment components (both quantitative and qualitative) will occur at 24 months post-baseline (2018). Our trial protocol has been registered and is available on ClinicalTrials.gov (NCT03237585). We did not make any important changes to the trial design after trial commencement.

#### Study setting

This trial is being carried out in four districts located in the Central Region of Ghana. Two districts are along the Coast while the other two are inland districts. Figure 1 shows the location of the Central Region on the map of Ghana and the location of the study sites (districts) relative to each other. The Central Region occupies an area of approximately 9,800 square kilometres, which is about 6.6% of the land area of Ghana [8,11]. About 63% of the region is rural and the population was estimated at 2,413,050 for the year 2013 with an annual growth rate of 3.1% and a population density of about 215 inhabitants per square kilometre [8,11]. Adult literacy rates in the region is around 50%, with more men literate (69.8%) than women (46.3%) in the region [11]. The region is predominantly Akan speaking (82.0%) with Fante being the indigenous dialect of most districts in the region [11]. Unemployment rate is 8.0% which is 2.4% lower than the national average [11]. The unemployment rate among women is 8.2% and this is about 0.4% higher than in men in almost all the districts in the Ghana. Agriculture is the main occupation and employs more than two-thirds of the work force in many districts. Cocoa and oil palm production are concentrated mainly in the inland districts while pineapple, grain production, and fishing are concentrated mainly in the coastal districts [11].

**Figure 1. F0001:**
[figure not shown]
Location of the 4 study sites (Districts) in the central region of Ghana.

#### Selection and randomisation of study sites

The selection of intervention and control districts was done using a census map of the Central Region that showed Inland and Coastal districts. After excluding some districts because of previous VAW-related intervention activities conducted by the Gender Studies and Human Rights Documentation Centre (Gender Centre; two inland and two coastal districts were then purposively selected as study sites. Designated sites are separated from each other by a geographical buffer (at least one district wide) to reduce the possibility of intervention diffusing into control districts (Figure 1). To randomise the districts, the names of the two Inland districts were written on a piece of paper and placed in a bag. One paper was blindly drawn from the bag and the selected district was assigned as an intervention district, while the other was designated as the control district. Clusters in the Ghana Demographic and Health Survey (DHS) are census listed localities with each locality comprising one or more Enumeration Areas (EAs). Within each selected district, a list of localities was obtained from the Ghana Statistical Service (GSS). All localities were allocated numbers, placed in a bag and blindly drawn. A total of 40 localities, (10 per district) were selected to serve as clusters. Since localities comprise several EAs, there was a second layer of stratification such that within each district, women and men participants were drawn from different localities(Figures 2a & b).

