### Sample size estimation

Our sample size calculation for a community RCT was defined at two levels, i.e. the level of randomisation – number of clusters randomised, and the level of data collection – number of individuals surveyed in each household. Using the method of Hayes and Bennet [12], we estimated sample size (i.e. the number of clusters required in each arm of treatment) for an unmatched cluster-randomised control trial. The calculation made the following assumptions. The proportion in the population that experience any form of IPV (emotional, physical, sexual violence, or all three forms). This estimate is based on national-level data from the 2008 GDHS which indicates that among ever-married women age 15–49 years, 34.9% have experienced violence (any form) committed by their husband/partner in the 12 months preceding the GDHS survey [8]. We powered the study to detect a 30% reduction in violence in the intervention arms and took alpha (ɑ) = 0.05 (two-sided), set power at 90% and estimated the coefficient of variation (k) between clusters (localities) for the outcome measure to be k = 0.20 based on district-level census data from the Central Region of Ghana [11]. We planned to oversample by 15% to allow for incomplete questionnaires. Based on these calculations, a minimum sample size of 820 women and 820 men from 40 clusters per trial arm were sampled at baseline and the same numbers will be sampled again in the post-intervention survey. This would imply 90% power to detect a significant change at the 5% level with a 20% reduction in IPV incidence.

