## Data analysis

The main trial analysis will be done by intention to treat. Thus, for intervention districts, data for all respondents will be included whether they report contact with the intervention or not. Any participant who responds affirmatively to any one of the five questions on physical IPV or three questions on sexual IPV in the past 12 months at end line data collection point will be deemed to be an incident case of IPV victimisation (if woman) or perpetration (if man). IPV incidence will be compared between the study arms. Generalised Linear Mixed model for binary outcome (logistic regression) will be used to compare women’s past year experience or men’s perpetration of IPV between the two arms at end-point, adjusting for baseline prevalence. All qualitative data will be coded, and thematic approach will be used to evaluate the impact of the interventions implemented within the communities.

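### Districts were allocated to arms, but the power calculation counts localities as the randomised clusters, so the stated 90% power does not hold for the allocation used

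*Protocol article*

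**What the plan says.** Under Selection and randomisation of study sites, the protocol article first chooses the districts: "two inland and two coastal districts were then purposively selected as study sites". It then describes the draw for the inland pair: "One paper was blindly drawn from the bag and the selected district was assigned as an intervention district", the other becoming control. The coastal draw is not described. After that, localities are drawn from a list within each district: "A total of 40 localities, (10 per district) were selected to serve as clusters". The Abstract gives the arm totals: "A total of 40 localities were selected to serve as clusters (20 per trial arm) with about 82 households per cluster recruited at baseline". Women and men were kept apart: "within each district, women and men participants were drawn from different localities".

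The Sample size estimation section describes its first level as the count of clusters that were randomised and uses the Hayes and Bennett method to find "the number of clusters required in each arm of treatment) for an unmatched cluster-randomised control trial". It sets k = 0.20 between localities, a two-sided 5% level and 90% power. It names a 30% reduction as the design effect and closes by claiming 90% power for a 20% reduction.

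The Data analysis section speaks of treated districts when it defines intention to treat: "Thus, for intervention districts, data for all respondents will be included whether they report contact with the intervention or not". It plans a logistic mixed model at endline, adjusted for baseline prevalence, and does not name the clustering level.

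**The concern.** The bag draw of localities is sampling, not allocation. No locality could have landed in a different arm from its district, so the allocated units number four, not forty. All localities in a district share its police, social welfare and health services, and staff of those agencies are themselves trained as part of the intervention. They also share the local economy. Variation at that level cannot be averaged out by adding localities, and the calculation contains no term for it.

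Two things are at stake. One is the stated power, which depends on the number of independently allocated units. The other is the reading of the primary result: with two districts per arm, a change affecting one whole district can look like an intervention effect.

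**Working it through.** **Inputs from the protocol article.** Control rate π0 = 0.349; reduction 30% (π1 = 0.2443) or 20% (π1 = 0.2792); k = 0.20; two-sided 5%; 820 women and 820 men per arm; about 82 per locality; 10 localities per district; 20 per arm.

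**Derived layout.** 20/10 = 2 districts per arm. 820/82 = 10 localities per arm for each sex, or 5 per district if split evenly (assumed).

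**1. The plan's own figure.** Clusters per arm:

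c = 1 + (1.960 + 1.282)² × [π0(1−π0)/m + π1(1−π1)/m + k²(π0² + π1²)] / (π0 − π1)²

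Taken literally, the section's closing figures are 40 clusters per arm and 1,640 people per arm, so m = 1,640/40 = 41. For a 20% reduction:

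- bracket = 0.00554 + 0.00491 + 0.00799 = 0.01844
- divided by 0.0698² = 0.00487 this is 3.785; times 10.507 it is 39.8; so c = 40.8
- power with c = 40 is 89.4%, which reproduces the stated 90%

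The 30% design effect also reproduces at about 35 completers per locality: c = 19.2, and power with 20 per arm is 91.1% (20 × 35/0.85 = 824, against 820). Both matches treat localities as independently randomised. The first also needs 40 localities per arm, whereas the article elsewhere gives 40 in total.

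**2. The described layout, localities still as the unit.** With m = 82, the same formula gives the following power.

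| | 10 localities per arm (one sex) | 20 per arm (pooled) |
|---|---|---|
| 30% reduction | 80.9% | 98.5% |
| 20% reduction | 44.5% | 75.4% |

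**3. Districts as the unit, no between-district variance.** The standard error of the arm difference is the square root of [k²(π0² + π1²) + π0(1−π0)/82 + π1(1−π1)/82]/n, with n = 10 (one sex) or 20 (pooled). For 30% and n = 10 this is √[(0.00726 + 0.00277 + 0.00225)/10] = 0.0350. The difference is 0.1047, so the noncentrality is 0.1047/0.0350 = 2.99. The critical t is 4.303 on 2 df and 12.706 on 1 df (two pair differences). Noncentral t power, endline only and without baseline adjustment:

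| | one sex, 2 df | pooled, 2 df | one sex, 1 df | pooled, 1 df |
|---|---|---|---|---|
| 30% reduction | 38.5% | 60.2% | 18.5% | 26.0% |
| 20% reduction | 20.6% | 33.7% | 12.1% | 16.9% |

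**4. Adding between-district variation (assumed; the article gives no value).** The variance gains k_d²(π0² + π1²)/2. On 2 df, power for a 30% reduction becomes 26% (one sex) or 33% (pooled) at k_d = 0.10, and 15% or 16% at k_d = 0.20. For a 20% reduction it becomes 14% or 18%, and 9% or 10%.

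**5. Randomisation p-value.** If the coastal pair was drawn like the inland pair, there are 2 × 2 = 4 allocations and the smallest two-sided p is 2/4 = 0.50. If allocation was unrestricted, there are 6 and the smallest is 2/6 = 0.33.

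**6. Error rate if locality were the only cluster level.** I simulated 2 arms × 2 districts × 5 localities × 82 people, no effect, and total between-locality variance (0.20 × 0.349)². The district shares are assumptions. The adjusted rows assume the same localities are surveyed twice and use a locality-level ANCOVA.

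| District share of between-locality variance | 10% | 20% | 30% | 50% |
|---|---|---|---|---|
| Endline t-test, unadjusted | 8% | 12% | 15% | 22% |
| Baseline-adjusted, true rates stable over time | 6% | 6% | 7% | 9% |
| Baseline-adjusted, correlation 0.8 over time | 7% | 9% | 11% | 15% |

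With a zero district share, all three are 5% within simulation error.

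**The case against.** The strongest reply concerns the error rate. A reader might infer that the planned analysis has an inflated type I error as a matter of fact. The article does not support that. It names a mixed model without its random-effect level, which may be settled in a fuller document, and it gives no between-district variance. It also adjusts for baseline prevalence, which removes much of any stable district difference; what remains is differential change. The unadjusted 8% to 22% is therefore an upper scenario. This objection stands.

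Three further readings also go too far:

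- **Power of 38.5% as a ceiling.** It is for one sex, endline only. Pooling gives 60%, and baseline adjustment might add precision by an amount the article does not allow one to calculate.
- **A p-value floor of 0.50 as a fact.** It rests on an inferred coastal draw.
- **k = 0.20 as a between-district figure.** It is said to be based on district-level census data, but the section defines it as between localities. The k_d = 0.20 case above is only the end of an assumed range.

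The plan also has real safeguards. The buffer at least one district wide is a sound reason to allocate by district, the sites are split into inland and coastal, and contact with other gender-based violence programmes is to be recorded. These limit contamination and help interpretation. They do not turn localities into allocated units or restore the 90%. A model with a district level would protect the error rate only by giving up the stated power.

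**Conclusion.** The article states the unit of randomisation wrongly in its sample size section, and the 90% power does not hold for the allocation it describes. This follows from the text and does not depend on an assumed variance. The inference is two districts per arm, from ten localities per district and twenty per arm.

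The size of the loss rests on the plan's inputs, endline data alone and no baseline adjustment. Even with identical districts, power for a 30% reduction drops to about 38.5% per sex or 60% pooled on 2 df. For the 20% reduction in the closing claim it is about 21% or 34%.

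The effect on the p-value is conditional. If the mixed model clusters on locality alone, its p-value is too small to the extent that districts differ in change over time. The article does not let that extent be measured, and four districts cannot usefully estimate it.

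The conflicts between 40 clusters in total and 40 per arm, and between a 20% and a 30% reduction, are separate faults and are not needed for this conclusion.

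**What to change.** - Describe the trial as four districts allocated, two per arm, with localities as sub-clusters sampled within them. State how the coastal pair was drawn.
- Withdraw the 90% power, or restate it for that design with its assumptions about between-district variation and baseline adjustment.
- Beside the model estimate, report the baseline-to-endline change in each of the four districts and the inland and coastal pair differences.
- Label any p-value or interval that rests on locality-level clustering as conditional on no between-district variation in change.
- State the four-district limit in the conclusions.

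Allocation and the baseline survey are already fixed, so the cost is wording and a little extra tabulation, with no new data. The price is a much less favourable power figure and a more cautious conclusion.

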**Figure 2. F0002:**
[figure not shown]
(a) Sampling strategy at baseline and post-intervention. (b) CONSORT diagram for participant selection in the localities.

#### Recruitment and inclusion/exclusion criteria

We recruited adult women (ages 18 to 49 years) and adult men (≥ 18 years) in the Central Region of Ghana. A multistage stratified cluster random sampling process was used to sample households (individuals) within selected communities at baseline and the same procedure will be repeated at endline. An overview of the randomisation and recruitment process is shown in Figures 2(a & b). In both Intervention and control districts, about 82 households were selected from 10 localities in each district. Sampling of households within a community was random and was done using a computerised system. In each selected household, one female or male subject was invited to participate in the trial. Individuals are eligible for inclusion in the study if they usually live (sleep and eat) in the household and lived in the community for at least a year. A limit of one respondent per household was set out of consideration for safety and confidentiality. All selected participants must be able to communicate in the main languages of the study (English, Twi, and Fante) and not be suffering from a mental deficit (learning difficulty, mental illness or substance abuse) which would impair their ability to consent to participation in the trial. E.g. individuals with psychosis cannot consent for research participation, but those with other mental illnesses, such as post-traumatic stress disorder or depression, would not be excluded. Furthermore, having consumed alcohol does not exclude a person from participating in the trial, it is only being currently drunk/drugged that stops consent being given. This inclusion/exclusion criteria are important in order not to bias the sample away from people who have experienced violence who may have substance abuse and other mental health problems.

